### Passive surveillance

The passive surveillance component of STRATAA is designed to capture cases of febrile disease occurring in each of the three census populations. Patients presenting to any of the clinical surveillance sites with a history of subjective fever >72 hours or objective fever >38.5°C on presentation will be approached for enrolment.

An index case will be defined as an individual with a blood culture result confirming infection with *S* Typhi or *S* Paratyphi A (or NTS in Malawi), and whose household is included in the census survey. These cases will be used to calculate the disease incidence in each of the three census sites. Consenting individuals will have samples of blood, urine and stool collected to determine a diagnosis of *S* Typhi, *S* Paratyphi A or NTS and to provide material for the further diagnostic and genetic aims of the study (see online supplementary table 1). Patients not resident in the census area will be enrolled as additional cases for the laboratory and genetic components of the programme if written consent is provided.

10.1136/bmjopen-2017-016283.supp1Supplementary data

### Healthcare utilisation and water, sanitation and hygiene surveys

To characterise the healthcare-seeking behaviour of individuals living in the census areas, at least 735 households will be randomly selected from the census area at each site to participate in a healthcare utilisation survey. Data will be collected from the head of the household/key informant to describe the actual and hypothetical usage of healthcare facilities for febrile episodes. The aim of this component is to estimate the per cent of cases (fulfilling the fever case definition) in each age stratum (0–4 years, 5–14 years and >14 years of age) who would or would not seek attention at one of the designated passive surveillance health facilities. Additional data regarding sanitation and hygiene facilities and usage will also be collected. Annual data collection periods will coincide with the peak typhoid season at each of the three sites.

### Serosurveys

To estimate the seroincidence and seroprevalence of clinical (both formally diagnosed and undiagnosed cases) and subclinical infection or exposure to *S* Typhi and *S* Paratyphi, systematic serosurveillance will be performed at each site. Blood samples will be collected at baseline and 3 months later, with sample collection initiated in an ongoing basis over the course of 1 year (table 3). To identify participants for the serosurvey, an age-stratified approach will be used to randomly select individuals from the census population from each age group. Suitable participants will be enrolled by field workers; where the individual identified is not available, a household member in the same age group will be selected. Where this is not possible, further households will be randomised into this component to ensure adequate numbers of individuals in the different age groups.

**Table 3 T3:** Sample size calculations for the serological surveys to estimate age-specific rates of high titres of serum IgG anti-H(d) antibodies

	Anticipated seroincidence (%)	Initial samples (n)	Anticipated number of events	Follow-up samples (n)*	Events detected (n)	Binomial exact (95% CI)	Probability of observing 0 events
0–4 years	0.2	2500	5	2000	4	0.0005 to 0.0051	0.0182
5–9 years	0.4	1300	5.2	1040	4	0.0010 to 0.0098	0.0155
10–14 years	0.8	800	6.4	640	5	0.0025 to 0.0181	0.0059
>14 years	0.2	3900	7.8	3120	6	0.0007 to 0.0042	0.0019
Total		8500	24.2	6800	19		

Assumes age-stratified individual sampling; also accounts for detection of 1% chronic carriage rate in those aged ≥10 years.

*Assuming 5% migration and 15% refusal.

Seroincidence (indicative of recent infection) will be calculated by measuring the rate of seroconversion to anti-H(d) (anti-flagellin) IgG and other acute-phase antibodies between both time points, with the denominator consisting only of individuals sampled twice and seronegative at the first time point.^56^

The seroprevalence of anti-Vi IgG will also be measured at baseline to identify individuals who could be potential chronic carriers. Previous studies have used high anti-Vi IgG antibody levels in serum as a marker of chronic carriage, and our aim is to use a recently validated/approved anti-Vi ELISA method to determine possible rates of chronic carriage across the three populations.^32 57 58^ In order to validate this method and to identify possible chronic carriers in the population (in addition to identifying whether there may be specific host genetic risk factors for chronic carriage), those individuals with a ‘high’ serum anti-Vi IgG titre will be reapproached and asked to provide two stool samples within 48 hours. With the agreement of relevant local ethics committees, identified chronic carriers (confirmed high anti-Vi IgG serum sample with a positive stool culture) will be treated with antibiotics for chronic carriage and clearance of bacterial shedding will be confirmed.

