To deliver on these objectives, the following studies will be performed in parallel at each of the three chosen field sites, starting in May 2016 with activities continuing until October 2018. First, in a well-defined population catchment of approximately 100 000 individuals, a detailed demographic census survey will be undertaken. Second, in healthcare facilities used by the census population (as confirmed through a healthcare utilisation survey) prospective passive surveillance to detect cases of enteric fever will be performed. Third, a seroincidence study will be conducted in an age-stratified sample of the census population at each site, collecting blood samples at intervals to estimate the rate of seroconversion to typhoidal *Salmonella* antigens and hence the rate of subclinical/asymptomatic exposure to these bacteria in the general population.

To meet the further objectives, which include evaluating diagnostic tests, identifying antimicrobial resistance patterns, exploring host susceptibility and bacterial virulence/genomic variation, biological samples, specimens and metadata will be collected during these individual studies. Data will be pooled to inform transmission dynamic and health economic models that can be used to help design future vaccine effectiveness studies and evaluate vaccine delivery strategies for widespread deployment.

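### Table 3 sizes the serosurvey on all 6800 paired samples, while the stated seroincidence analysis uses only pairs seronegative at the first sample, so the planned precision is somewhat too favourable

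*Protocol article*

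**What the plan says.** Blood is taken at baseline and 3 months later. Table 3 in the Serosurveys section is headed "Sample size calculations for the serological surveys to estimate age-specific rates of high titres of serum IgG anti-H(d) antibodies". For each age group it gives, in order, the anticipated seroincidence (%), initial samples, anticipated events, follow-up samples, events detected, exact 95% interval and probability of no events. The row for the youngest children reads "0–4 years 0.2 2500 5 2000 4 0.0005 to 0.0051 0.0182". The two middle groups, with anticipated seroincidence of 0.4% and 0.8%, have 1040 and 640 people followed up and 4 and 5 events respectively. The row for the oldest group, which has the largest sample, reads ">14 years 0.2 3900 7.8 3120 6 0.0007 to 0.0042 0.0019".

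The totals are 8500 initial samples, 6800 follow-up samples and 19 events detected. The footnote to the follow-up column attributes the whole reduction to 5% migration and 15% refusal.

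The text below the table defines seroincidence as the rate of seroconversion to anti-H(d) IgG and other acute-phase antibodies between the two samples, "with the denominator consisting only of individuals sampled twice and seronegative at the first time point". The section on rationale and aims says that the seroconversion rate will be estimated and "hence the rate of subclinical/asymptomatic exposure to these bacteria in the general population".

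**The concern.** The sample-size table and the analysis sentence use different denominators. The table keeps everyone who gives a second sample. The analysis then removes everyone already seropositive at the first, and no allowance is made for that loss.

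The two agree only if baseline anti-H(d) seropositivity is zero. The document's own description of the setting argues against that. The account of the Patan site calls natural exposure and subclinical infection common. The background section on burden and diagnostics refers to earlier surveys of the age-stratified prevalence of antibody to this same flagellar antigen.

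Each stratum expects only 4 to 6 events, so any loss of denominator shows up in the interval and in the chance of seeing none. A reader would take Table 3 as the precision of the planned estimate, but it belongs to a different denominator.

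**Working it through.** **Inputs.** Seroincidence p, initial and follow-up n, and the 5% and 15% losses all come from Table 3. The baseline seropositive share s is not in the documents and is assumed throughout.

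**Step 1: reproduce Table 3.**

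- Follow-up n = initial n × (1 − 0.05 − 0.15): 2500 × 0.80 = 2000; 1300 × 0.80 = 1040; 800 × 0.80 = 640; 3900 × 0.80 = 3120.
- Expected events = n × p: 4.00, 4.16, 5.12 and 6.24, total 19.52. The table rounds these to 4, 4, 5 and 6.
- Exact (Clopper-Pearson) 95% intervals: 4/2000 gives 0.00055 to 0.00511; 4/1040 gives 0.00105 to 0.00982; 5/640 gives 0.00254 to 0.01814; 6/3120 gives 0.00071 to 0.00418. All match.
- Probability of no events = (1 − p)^n: 0.998^2000 = 0.0182; 0.996^1040 = 0.0155; 0.992^640 = 0.0059; 0.998^3120 = 0.0019. All match.

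Other readings fail. Multiplicative loss (0.95 × 0.85) gives 2018.75 in the first row. Using the initial n gives a zero-event probability of 0.0067 there. The Poisson form misses in three of four rows. The table's arithmetic is therefore correct, and its denominator is all pairs (s = 0).

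**Step 2: apply the stated denominator.** Replace n by n × (1 − s), hold p at the Table 3 values, and recompute events and (1 − p)^(n(1 − s)).

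| Assumed s | Pairs | Expected events | P(0 events): 0–4 / 5–9 / 10–14 / >14 |
|---|---|---|---|
| 0 (Table 3) | 6800 | 19.5 | 0.018 / 0.015 / 0.006 / 0.002 |
| 10% uniform | 6120 | 17.6 | 0.027 / 0.024 / 0.010 / 0.004 |
| 20% uniform | 5440 | 15.6 | 0.041 / 0.036 / 0.016 / 0.007 |
| 30% uniform | 4760 | 13.7 | 0.061 / 0.054 / 0.027 / 0.013 |
| 2/8/18/33% by age | 5532 | 16.1 | 0.020 / 0.022 / 0.015 / 0.015 |

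Intervals at ages 0–4: s = 10% gives 4/1800, 0.0006 to 0.0057; s = 30% gives 3/1400, 0.0004 to 0.0062. Table 3 states 0.0005 to 0.0051.

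**Step 3: where the age-rising row comes from.** It uses Table 3's own rates, read as per 3-month interval, constant over life and with no waning, at assumed representative ages of 2.5, 7.5, 12.5 and 30 years:

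- 1 − 0.998^10 = 0.020
- 1 − 0.998^20 × 0.996^10 = 0.077
- 1 − 0.998^20 × 0.996^20 × 0.992^10 = 0.182
- 1 − 0.998^20 × 0.996^20 × 0.992^20 × 0.998^60 = 0.330

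Waning, or rates meant per year, would lower these shares. Cross-reactive antibody would raise them.

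**The case against.** **The effect may be small.** The table's title concerns high titres and the text speaks of recent infection, so the cut-off may be high and few people may be positive at baseline. At s = 10% the rounded events stay at 4, 4, 5 and 6 and the intervals widen only slightly. With shares derived from the table's own rates, no zero-event probability exceeds about 0.022. This limits the size of the problem but does not remove it.

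**A seronegative denominator is the ordinary definition of seroconversion.** It is, and the rationale section names seroconversion as the quantity measured. The rule itself is not at fault. The faults are that the sample-size table does not follow it, and that the result is a rate among seronegatives, one step short of exposure in the general population.

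**Only planning is affected.** Table 3 supports a secondary objective and no hypothesis test, and the final intervals will use the actual denominators. This is right, and it bears on severity.

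Three stronger readings are tempting but unsupported:

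- A reader might infer that the rule biases exposure downward and distorts the age pattern. Baseline seropositives leave both numerator and denominator, so the direction depends on their infection rate relative to seronegatives. The documents do not give it. If antibody marks immunity, the seronegative rate would exceed the population rate.
- A reader might infer that reinfections are lost altogether. A titre rise in someone still seropositive cannot count, but reinfection after reversion to seronegative can.
- A reader might assume seropositivity of 30% to 50% and conclude that the design fails. Nothing in the documents supports those shares. For ages 0–4, 30% is about 15 times the 2% implied by Table 3's own rates.

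**Conclusion.** The mismatch is real and sits within one section: Table 3 describes all pairs, while the analysis uses seronegative pairs. It stands whether the anticipated rates are meant per seronegative person, when n should be the seronegative pairs, or per person sampled, when the rates do not fit the analysis denominator.

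The stated precision is somewhat too favourable for the stated estimator. Over assumed shares of 10% to 30%, expected events are 10% to 30% below Table 3's; the age-rising case is about 17% below (16.1/19.5 = 0.83). These figures rest on the assumed s and on holding the anticipated rates fixed. This is a moderate point that should be corrected, but it does not threaten the primary burden objective.

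**What to change.** Add a column to Table 3 with an assumed seronegative fraction for each age group, give its source, and show a low-to-high range. Recompute the denominators, expected events, exact intervals and zero-event probabilities from it. In the Serosurveys and rationale text, describe the result as the seroconversion rate among people seronegative at baseline, and state what further assumption is needed to read it as general-population exposure.

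A prespecified fold-rise analysis in all pairs could be added as a secondary or sensitivity estimate. It need not be primary: it counts a different event, and Table 3's anticipated rates would not carry over to it.

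The cost is one revised table and a few reworded sentences, with slightly less favourable stated precision. No extra sampling is required unless the sponsor wants to keep the present precision. That would take 8500/(1 − s) initial samples at a uniform share: 8500/0.9 = 9444 at 10%, or 8500/0.7 = 12 143 at 30%.

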Furthermore, while using these new diagnostic tests in comprehensive passive surveillance or even active surveillance programmes will identify acute cases of typhoid disease, the incidence rate of subclinical infection and exposure is unknown. These data are likely essential to understanding pathogen transmission as well as the development and maintenance of immunity against clinical disease^12^ and are likely only to be obtainable through the use of seroepidemiological methods. Previous seroepidemiological studies have examined the cross-sectional age-stratified prevalence of antibodies to the *S* Typhi flagellar (H) antigen in Santiago, Chile,^28^ and serum bactericidal antibody in Kathmandu, Nepal.^29^ Also, high-antibody titres to the Vi (Vi capsular polysaccharide; virulence factor) antigen of *S* Typhi measured by agglutination assay have been used to estimate chronic carrier frequency in population-based studies,^30–32^ although these studies were not universally successful at identifying chronic carriers.^33^ Improvements in serological assays and the discovery of a newer generation of diagnostic antigens^34^ suggest that population-based serosurveillance studies, especially using longitudinal measurements, may provide key data regarding the incidence of subclinical infection with the bacterial agents of enteric fever and the prevalence of chronic carriers.

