### Household contacts

To further investigate possible transmission links, household contacts of index cases presenting with blood culture-confirmed *S* Typhi or *S* Paratyphi A infection will be identified through the census data collection and approached to take part in this component of the study. Up to five members of the household, with consent, will be asked to provide a blood and stool sample at the time of discharge of the index case, a further stool sample at 1 month and repeat serology at 6 months (see online supplementary table 1), and asked about the occurrence of symptoms. These samples will be investigated to identify those with subclinical infection or possible chronic carriers. Secondary attack rates for the occurrence of symptomatic infection will be estimated. If serology suggests chronic carriage in a household contact, additional blood and stool samples will be collected to confirm this, and antimicrobial treatment to eradicate carriage will be proposed.

Those individuals who are identified as shedding bacteria but without high serum anti-Vi IgG levels will be followed up at a 1-year interval to repeat stool culture. Repeat blood samples will be collected from household contacts approximately 3 months after initial sampling to explore whether rates of seroconversion are higher in these individuals compared with those in the general population. At least 73 households of index cases are expected to be enrolled in this component of the study.

In a similar approach to the acute cases of typhoid infection, where chronic carriers are identified from the serosurveys, household transmission studies will be performed among household contacts of possible chronic carriers (ie, those with a ‘high’ serum anti-Vi IgG titre). A one-time attempt will be made to enrol up to five members of the household, sampling serology and stool looking for evidence of typhoid infection. This will provide data on secondary attack rates for both acute and chronic typhoid states.

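### Serosurvey stool is cultured only from people with a high anti-Vi titre, so the survey can give the positive predictive value of that titre but not its sensitivity or the true carriage prevalence

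*Protocol article*

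**What the plan says.** All references are to the protocol article.

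- **Serosurveys, purpose.** Anti-Vi IgG is measured at baseline, and the ELISA is to be used "to determine possible rates of chronic carriage across the three populations". Stool sampling is introduced with the words "In order to validate this method and to identify possible chronic carriers in the population".
- **Serosurveys, who is cultured.** Only people with a high anti-Vi IgG "titre will be reapproached and asked to provide two stool samples within 48 hours". No stool is planned from serosurvey participants without a high titre.
- **Serosurveys, identified carrier.** The sentence on treatment describes such a person by a "confirmed high anti-Vi IgG serum sample with a positive stool culture".
- **Table 3, footnote.** The sample size "also accounts for detection of 1% chronic carriage rate in those aged ≥10 years".
- **Household contacts.** Contacts of index cases, and of people with a high titre, are asked for blood and stool whatever their own titre. Contacts found "shedding bacteria but without high serum anti-Vi IgG levels will be followed up at a 1-year interval" for repeat stool culture.
- **Burden of disease and diagnostics.** Earlier population studies used high anti-Vi titres to estimate carrier frequency, "although these studies were not universally successful at identifying chronic carriers".

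**The concern.** Validating a marker normally means learning how often it is right in both directions: among those it flags and among those it does not. Here the reference test, stool culture, is applied only to those it flags. A carrier with a low titre leaves no trace in the serosurvey. The article accepts elsewhere that such people may exist, since it reports that anti-Vi has not always found carriers and it plans follow-up for low-titre shedders among contacts.

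This is not a detail that an analysis plan could supply later, because the stool that would be needed is never collected. The stake is how the number is read. The rationale section says the data will parameterise and validate transmission models, and the Discussion lists the contribution of carriers to transmission among the gaps to be filled. A rate found by screening, if entered as the population carriage rate, would carry an error that nothing in the serosurvey could reveal.

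**Working it through.** **1. The plan's own figures.** Table 3 reproduces.
- Follow-up n = initial n × (1 − 0.05 − 0.15), from the footnote "Assuming 5% migration and 15% refusal". This gives 2000, 1040, 640 and 3120, total 6800.
- Exact (Clopper–Pearson) intervals for 4, 4, 5 and 6 events are 0.0005–0.0051, 0.0010–0.0098, 0.0025–0.0181 and 0.0007–0.0042, as printed.
- P(0 events) = (1 − p)^n gives 0.0182, 0.0155, 0.0059 and 0.0019, as printed.

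The arithmetic is sound. The problem lies in who is cultured.

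**2. Expected carriers.** Baseline samples at age 10 or over: 800 + 3900 = 4700, read as per site. At 1% carriage that is 47 carriers (exact 95% CI 0.74% to 1.33%).

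**3. What the observed data can distinguish.** Assume 3% have a high titre (141 of 4700) and 35 of them are culture-positive, which is about 47 × 0.75. Both are assumptions, since the article gives neither figure. Let c be the unseen number of low-titre carriers, and take culture as the reference.
- Positive predictive value = 35/141
- Sensitivity = 35/(35 + c)
- Specificity = (4700 − 141 − c)/(4700 − 35 − c)
- Prevalence = (35 + c)/4700

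| c (never observed) | PPV | Specificity | Sensitivity | Prevalence |
|---|---|---|---|---|
| 0 | 24.8% | 97.73% | 100% | 0.74% |
| 12 | 24.8% | 97.72% | 74% | 1.00% |
| 35 | 24.8% | 97.71% | 50% | 1.49% |
| 100 | 24.8% | 97.68% | 26% | 2.87% |

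The serosurvey data are identical in all four rows. The predictive value is fixed and specificity moves by 0.05 percentage points. Sensitivity and prevalence are not determined.

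**4. Which way the confirmed rate errs.** For carriers alone, expected confirmed rate = prevalence × anti-Vi sensitivity × culture sensitivity. At 1% prevalence and assumed sensitivities this is 0.75% (75% and 100%), 0.60% (75% and 80%) or 0.25% (50% and 50%).

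Two stools within 48 hours, however, cannot exclude transient shedding. Let s be the anti-Vi sensitivity and f the share of culture-positive, high-titre people who are transient shedders. With perfect culture, true chronic carriage ÷ confirmed rate = (1 − f)/s. This exceeds 1 when f < 1 − s and is below 1 when f > 1 − s; at s = 75% the two errors cancel at f = 25%. The confirmed rate is therefore a lower bound on culture-detectable shedding, because high-titre shedders are a subset of all shedders. For chronic carriage the direction is not known.

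**5. Whether household contacts can fill the gap.** At the stated minimum of 73 index households, with all five contacts enrolled in each, there are 73 × 5 = 365 people. At 1% carriage and 75% sensitivity (assumed), the expected number of low-titre carriers is 365 × 0.01 × 0.25 = 0.91, and P(0) = (1 − 0.0025)^365 = 0.40. No number is given for contacts of high-titre people. Both groups are selected by exposure.

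**The case against.** The strongest reply is that the article claims little. It speaks of possible rates and possible carriers, calls the ELISA already validated or approved, and uses a feasible two-stage design of serology followed by culture of positives. Culturing screen-positives is a form of field validation. Carriage is not named among the Table 1 objectives. Much of this stands, and it limits the point. It does not remove it, because validation is still given as a purpose of the stool sampling and the rates are still described as applying to the three populations.

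A reader might infer more than the documents support:

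- *That the test cannot be validated at all, or that specificity is out of reach.* The predictive value can be estimated, and step 3 shows that specificity is tightly bounded when carriage is rare.
- *That sensitivity is 100% by construction because anti-Vi is part of the carrier definition.* That definition stands in a sentence about treatment, and the article nowhere says that sensitivity will be computed against it. Within the serosurvey it adds nothing to the fact that only high-titre people are cultured.
- *That chronic carriage is understated by a factor of 1.1 to 2.0.* That is 1/0.9 to 1/0.5, from an assumed sensitivity of 50–90%. It ignores transient shedding, which pushes the other way. The 1% in Table 3 may also already mean the detectable rate.
- *That missed carriers would be modelled as absent.* The article says only that data will be pooled to inform models.
- *That the household contacts supply the correction.* Step 5 shows that they are too few and too selected.

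**Conclusion.** The point holds in limited form. As written, the serosurvey is given a validation aim that its stool sampling can meet only in part. It yields the positive predictive value of a high anti-Vi titre among those who give stool, and a near-exact specificity if carriage is rare. It does not yield sensitivity or true carriage prevalence.

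In the illustration, the same data fit a sensitivity anywhere from 26% to 100% and a prevalence from 0.74% to 2.87%. Those figures rest on an assumed 3% high-titre share and 35 culture-positives. The lack of identification does not depend on them, since it follows from the absence of any low-titre stool. No particular size or direction of error in the chronic carriage rate can be claimed from the documents.

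**What to change.** 1. In Serosurveys, replace the aim of validating the method with that of estimating the positive predictive value of a high anti-Vi titre.
2. Report the serosurvey result as the prevalence of high-titre, culture-positive individuals. State that it is a lower bound on culture-detectable shedding and not an unbiased rate of chronic carriage, for two reasons: low-titre carriers are missed, and two stools within 48 hours cannot exclude transient shedding.
3. Carry this into the transmission model as a sensitivity analysis over a stated, assumed range of anti-Vi sensitivity, for example 50–100%.
4. Describe anti-Vi results in culture-positive household contacts, but do not use them to correct the carriage rate.

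None of this alters sampling or care. The cost is wording, a few model runs and a less definite carriage estimate.

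Only stool from a random sample of low-titre participants would identify sensitivity, and I do not ask for it. Under the assumptions above, 1000 such people would be expected to yield only 2.6 positives at 75% sensitivity (P(0) = 0.08), or 5.2 at 50%.
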